#### Patients

Eligible patients must be women aged 18 to 50 years, fertile, English-speaking, and able to provide informed consent. They must also meet at least one of the following criteria: (1) a documented medical condition or multiple medical conditions being *actively managed* (on medication or requiring at least 2 visits a year), (2) a documented past medical condition or multiple medical conditions which would pose a significant risk to health during pregnancy (eg, past lung clot), or (3) current use of any drugs that are Pregnancy Category D or Category X medications. This definition expands upon guidance provided by the Department of Health and Human Services [67] as well as informed by pilot interviews with 15 PCPs (unpublished data). To obtain a range of perspectives, we aim to sample approximately equal numbers of women in the following groups that consist of conditions commonly encountered in primary care [68], conditions that frequently coexist together, or are managed with similar behavioral approaches and medications. Furthermore, we will focus on conditions for which there is evidence-based guidance regarding contraceptive selection in the CDC US MEC [69]. The following groups are described in detail in Multimedia Appendix 1: (1) psychiatric conditions, (2) metabolic and endocrine conditions, and (3) neurologic conditions. We will include an *other* group to capture women with less common conditions that nevertheless have a significant impact on pregnancy-related morbidity and mortality and contraceptive eligibility. The principal investigator (JW), who is a primary care specialist and a family planning expert, will review each participant’s medical history and medications, in conjunction with the designated practice liaison, to ensure that eligibility criteria have been met.

The designated practice liaison in each practice will assist the study team in identifying patients who meet the eligibility criteria. With the permission of their PCPs, recruitment letters will be sent to potentially eligible patients followed up by up to 3 phone calls.

### Context Assessment Frameworks to Guide Implementation (Practice and Provider Level)

Dehlendorf and colleagues recently described the development and testing of a tablet-based contraceptive decision aid that underwent rigorous cognitive testing [70] among patients in a safety net clinic. Our adaptation of this decision aid model will be sensitized by the application of our data to selected constructs from the CFIR, a typology of 5 major domains and associated constructs to assess context [59]. We chose CFIR because it identifies constructs at the practice and provider level that are universally relevant to successful implementation of a new intervention in clinical practice and can be tailored to the context of contraception. Furthermore, we anticipate that the use of CFIR will facilitate the collection of qualitative and quantitative data in a harmonized and efficient manner. Because the proposed intervention integrates clinical decision support for individual health providers, we also adapted constructs from the Theoretical Domains Framework to systematically identify determinants of clinical behavior change among PCPs [71]. We created a mixed methods theory-data matrix (see Multimedia Appendices 2-4), CSIR constructs and definitions by Damschroder et al [59]) to summarize how qualitative data (derived from practice observation, artifacts, and interviews) and quantitative data (derived from surveys) map to CFIR and Theoretical Domains Framework constructs (see Multimedia Appendices 2-4).

**Conceptual Model to Guide Development of the Decision Tool (Patient-Level)**

In a systematic review, Wyatt and colleagues identified 32 unique characteristics among 19 decision aids and classified them into 4 overarching categories: method effect, mechanistic, social/normative, and practical [72]. Among these attributes, studies have shown that women prioritize knowledge regarding mechanism of action [44], contraceptive effectiveness, safety, and side effects [73]. Using the tablet-based decision aid described by Dehlendorf as the prototype model [70], we will customize the above high-priority attributes for this patient population. Using a drop-down menu function, women will first provide their basic health history, including age, smoking status, medical conditions, and medications. We will then elicit patient preferences, guided by a conceptual model that incorporates a synthesis of constructs from reproductive justice theory, behavioral health theories, and evidence-based counseling techniques such as motivational interviewing and values clarification (Figure 2). One of the central tenets of reproductive justice is that people should be equally afforded the right to have a child and parent as well as the right to not have a child [74]. In accordance with this principle, we assert that a patient-centered contraceptive tool must be designed to prevent unconscious or conscious reproductive coercion, particularly toward individuals from marginalized communities. This concern is based upon the disturbing legacy of compulsory sterilization programs that targeted women of color, poor women, women with disabilities, and immigrant women in multiple US states throughout the twentieth century [75] and even as recently as 2010 in California [76]. Therefore, the model explicitly avoids presumptions about the patient’s feelings regarding pregnancy and childbearing and starts with a values clarification [77] question by asking the patient about her current feelings regarding pregnancy and parenting.

**Figure 2 figure2:**
[figure not shown]
Conceptual model to guide design of decision tool. PCP: primary care provider; CDC: Centers for Disease Control and Prevention.

Adapting a principle from the transtheoretical model [78], the patient will receive recommendations that are “matched” to her current pregnancy desires. If she does not want to get pregnant *and* indicates she is ready for contraceptive education, she will proceed through a responsive algorithm based upon her personal preferences, concerns, and prior contraceptive experiences. Constructs from the health beliefs model [79] will be operationalized to provide her information regarding the potential impact of her chronic condition on her reproductive health and vice versa, as well as individualized pros and cons of different contraceptive methods. The decision tool will summarize her preferences for methods, concerns she may want to discuss with her PCP, and embed clinical decision support for the PCP based upon the US MEC Guidelines (eg, patient has severe diabetes and should not use estrogen). This information will be made available in paper or electronic form to serve as a template for provider-patient discussion during the office visit.

If the patient indicates she desires pregnancy, she is advised to return to her PCP for preconception counseling and exits the study at this time. If the patient expresses ambivalence regarding pregnancy, the decision aid assesses if she is ready for contraceptive education, and if so, she proceeds through the contraceptive algorithm as outlined above.

### Data Collection

Trained research assistants (RA) will spend 2 to 3 days at each clinical site to collect practice-specific data using a Practice Environment Template (PET), a semistructured checklist adapted from prior work by Crabtree and colleagues [80] and Jaén and colleagues [81]. The PET cues the RA to record observations of routine office activities, with a focus on clinical flow and processes relevant to contraceptive services. These data will provide a more complete and nuanced description of “what is happening on ground” and identify data that participants may not report on surveys or during interviews. The designated practice liaison will complete the Practice Information Form, a 29-item survey, also modified from prior work [80,81], that consists of multiple choice and open response items regarding practice demographics, pay structure, preventive and reproductive health services offered, and contraceptive methods offered.

All participants (staff, PCPs, and patients) will fill out a written or electronic (via Qualtrics, Provo, UT) quantitative survey before the face-to-face in-depth interview. There are 3 surveys: (1) a 34-item Patient Survey, (2) a 19-item Provider Survey (for PCPs), and (3) a 13-item Staff Survey (for practice members other than PCPs). Participants will be interviewed in a quiet, private space designated by each practice. Interviews are audiotaped with the participants’ permission and informed consent. We will conduct “member checking” with participants who agree to be contacted after the interview. This qualitative technique, also referred to as respondent validation, helps improve the accuracy, credibility, and transferability of research findings as well as empower participants to verify or modify the final interpretations of the data [61]. Member-checking should be undertaken with caution to minimize the risk of participant discomfort and ensure anonymity [82]. Therefore, we will share general themes and aggregated group data rather than specific quotes from individuals. All participants who complete an in-depth interview will receive a US $30 gift card as a token of appreciation for their time.

### Data Analysis

All interview audiotapes will be transcribed verbatim. Qualitative analysis is an iterative process during which investigators go through cycles of reading, summarizing, and re-reading data [83,84]. The qualitative team is composed of 4 individuals from different professional backgrounds and research disciplines, including family medicine, dentistry, epidemiology, and health behavior. Though all team members identify as female, they vary in age, sexual orientation, religious background, and race/ethnicity. The interview transcripts will be uploaded and organized using MAXQDA software (VERBI GmbH, Berlin, Germany Version 12.3.1). We will conduct analysis through a series of iterative steps adapted from techniques described by Marshall and Rossman [85]. First, each team member will review several transcripts independently and code the content of each transcript. Because our research design is driven by predetermined theoretical constructs and research aims, our initial coding will be done with a theory-generated code template [86]. In vivo coding will also occur as new themes emerge from the interviews [85]. The team members will discuss, compare, and reconcile differences in coding and create a consensus code template, which will then be used to code the remainder of transcripts. Analysis of semistructured observations and practice artifacts proceeds in similar manner as described for interview transcripts. Themes and patterns will be identified and synthesized, using the preidentified theoretical constructs as a guide (Multimedia Appendices 2-4), as well as new codes and themes as they emerge. To increase the trustworthiness of our qualitative findings, we will triangulate our qualitative findings on multiple levels [54]: (1) methodological triangulation, by comparing and integrating with quantitative survey data, (2) data triangulation, by comparing and contrasting data obtained via interviews, surveys, observations, and artifacts, and (3) theoretical triangulation, by gathering multiple perspectives of the same phenomenon (patient-, provider-, practice-level perspectives). Data collection continues until saturation is reached, or until we no longer identify new or disconfirming or confirming data [84] with respect to the original research aim. Quantitative survey data will be summarized with simple descriptive statistics (frequencies, means, and SDs). We will conduct bivariate analyses with Fisher exact test to explore the following relationships: (1) demographic traits of providers and their contraceptive recommendations and practices, (2) practice attributes and providers’ contraceptive recommendations and practices, (3) the presence of different chronic conditions and current pregnancy desires among women, and (4) the presence of different chronic conditions and current contraceptive use among women. As described by Fetters [60], we will merge the quantitative and qualitative strands of data by identifying content from both datasets to compare, contrast, and synthesize. A final interpretation will summarize to what extent and how the results from the qualitative and quantitative data contribute to the identification of patient-, provider-, and practice-level factors that will then shape the design and implementation of the decision tool.

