### Sampling Strategy, Eligibility, and Recruitment

#### Practices

To balance similarity and variation across practices, providers, and patients, we will use a combination of purposeful sampling techniques as described by Palinkas and colleagues [62]. Eligible practices include practices that identify as family medicine, internal medicine, internal medicine-pediatric, or any combination of these. First, we will use criterion sampling to select individuals who have experiences that are relevant to the phenomenon of interest [62]; for this study, we aim to select practices for which a contraceptive intervention is both clinically relevant and feasible to implement. Because LARC methods (intrauterine device and implant) are the most effective reversible methods and medically appropriate for the vast majority of women with chronic conditions [36,37,63], we will recruit practices that either provide LARC or assist with referrals for LARC. Therefore, eligible practices must have: (1) one or more providers who currently offer prescription contraception (eg, oral contraceptive pills), and (2) informal or formal processes to refer patients who desire LARC methods to another site *or* provide LARC methods on site. To achieve maximum variation in practice attributes that are associated with variations in contraceptive practice [31,64], clinical sites will be sampled to reflect a range of location (urban, suburban, and rural practices), a balance between private practices and practices with federal designations (federally qualified health centers, rural health center, medically underserved areas), and diversity in the racial/ethnic background of patients. Thus, maximum variation sampling aims to achieve breadth in sampling and can highlight differences between practices. To complement this approach, we will also use snowball sampling such that participating practices suggest other practices for recruitment; this approach tends to select practices that share characteristics and thus will help to achieve depth of understanding of similar practices [62]. We will recruit practices through The Great Lakes Research Into Practice Network, a statewide practice-based research network that is recognized by the Agency for Healthcare Research and Quality [65].

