#### Sample Size

To achieve the depth and variation in practices as described above, we aim to enroll 6 clinical sites. For individual qualitative interviews, prior literature has documented that 6 to 12 interviews per homogeneous group provide sufficient qualitative data to reach saturation, the point at which analysis produces no new information, or disconfirming or confirming evidence [55,66]. On the basis of the sampling strategy described, we aim to enroll 30 patients, 30 PCPs, and 30 staff members (nurses, medical assistants, and administrative staff). Our definitions of homogenous groups are summarized below and in Multimedia Appendix 1. Purposeful sampling will be driven by this matrix such that the perspectives of individuals in each category are represented in qualitative interview data with the goal of data saturation. We expect this category to evolve based upon patient population characteristics in recruited practices.

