#### Practice Members (Primary Care Practices and Staff)

Eligible practice members must be aged 18 years or older, English-speaking, able to give informed consent, and be indirectly or directly involved with patient care. PCPs must be physicians, nurse practitioners, physician assistants, or certified nurse midwives, who currently provide preventive health and management of chronic conditions to reproductive-aged women [62]. To complement criterion sampling as described above, we seek maximal variation [62] in PCPs’ contraceptive practices and will sample individuals who: (1) do not provide prescription contraception (eg, oral contraceptive pills), (2) provide prescription contraception but *do not* insert LARC devices, or (3) provide prescription contraception *and* insert LARC devices. For practice staff members other than PCPs, we aim to gather staff perspectives regarding contraceptive services and interventions that may differ based upon their primary responsibilities and context of patient interaction: (1) director or manager (clinical director, administrative director, nurse manager), (2) work with PCPs during clinical visits (nurses, medical assistants, licensed practical nurses), and (3) other services (social work, complex care management, pharmacist, behavioral counselor). A designated practice liaison (eg, medical director, office manager) will assist the study team to identify eligible practice members and extend invitations for study participation.

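### The provider-level Fisher exact test for practice attributes treats about 30 providers in 6 practices as independent, so its p-values can overstate the evidence

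*Protocol article*

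**What the plan says.** All references are to the protocol article.

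- **Data Analysis** names the test: "We will conduct bivariate analyses with Fisher exact test to explore the following relationships". Relationship (2) is "practice attributes and providers’ contraceptive recommendations and practices".
- **Sample Size** sets the number of practices, "we aim to enroll 6 clinical sites", and of individuals, "we aim to enroll 30 patients, 30 PCPs, and 30 staff members". These numbers rest on qualitative saturation. No power, effect size, significance level or ICC is given.
- **Data Collection** has practice data recorded once per site: "The designated practice liaison will complete the Practice Information Form, a 29-item survey".
- **Practices** (under Sampling Strategy) selects sites for "maximum variation in practice attributes that are associated with variations in contraceptive practice".
- **Practice Members** adds, for providers, that "we seek maximal variation [62] in PCPs’ contraceptive practices".

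The article describes no practice-level analysis or allowance for clustering, and it gives no caution about reading these p-values. The limitations in the Discussion do not mention the matter.

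**The concern.** Fisher's test takes each provider as a separate, independent observation. In relationship (2) the explanatory variable belongs to the practice, and all providers at a site share it. If they also resemble each other in what they recommend or do, a chance difference between a few sites looks like a difference between many independent providers.

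The article gives reason to expect such resemblance. It samples practices on attributes that it says go with differences in contraceptive practice. Eligible sites either provide long-acting reversible contraception (LARC) or refer for it, and one provider behaviour of interest is whether the PCP inserts devices. That outcome is likely to differ sharply between sites.

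At stake is the quantitative contribution to the list of practice-level factors that will shape the decision tool. The survey results are also used to triangulate the qualitative themes, so a p-value that is too small could seem to corroborate a theme when it does not.

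**Working it through.** The article states no statistical figure for this analysis, so there is none to reproduce.

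**Inputs from the article.** 6 practices, 30 PCPs, a Fisher exact test, and practice attributes recorded once per site.

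**Assumptions.** Equal spread, 30/6 = 5 PCPs per practice. Two-sided nominal level 0.05. Binary attribute splitting the practices 3 v 3 or 2 v 4. ICC from 0 to 0.5.

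**Step 1: information lost to clustering.** Design effect = 1 + (5 − 1) × ICC; effective number = 30 / design effect.

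| ICC | Design effect | Effective number of PCPs |
|---|---|---|
| 0 | 1.0 | 30 |
| 0.1 | 1.4 | 21.4 |
| 0.2 | 1.8 | 16.7 |
| 0.3 | 2.2 | 13.6 |
| 0.5 | 3.0 | 10 |
| 1 | 5.0 | 6 |

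**Step 2: false-positive rate of the planned test.** Beta-binomial outcome with proportion 0.5, no true attribute effect, 100,000 simulated studies per setting:

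| ICC | 3 v 3 practices | 2 v 4 practices |
|---|---|---|
| 0 | 1.7% | 2.6% |
| 0.05 | 3.0% | 4.5% |
| 0.1 | 4.5% | 6.4% |
| 0.2 | 8.0% | 10.9% |
| 0.3 | 11.8% | 15.7% |
| 0.5 | 19.9% | 24.7% |

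Exact enumeration of the same model agrees to within 0.2 percentage points. At a proportion of 0.3 the 3 v 3 results are almost identical, and the 2 v 4 results run from 3.1% to 22.3%. Fisher's test is conservative at this size. It therefore stays within 5% up to an ICC of about 0.1 (3 v 3) or 0.05 (2 v 4).

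**Step 3: what the test cannot see.** Suppose 12/15 providers in three practices and 5/15 in the other three report a behaviour. Fisher gives p = 0.025 however the counts fall by practice.

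- Counts 4, 5, 3 against 1, 2, 2: practices within a group agree. A practice-level t-test on the proportions gives t = (0.80 − 0.33)/0.133 = 3.5 on 4 df, p = 0.025. Exact permutation of practices gives 2/20 = 0.10.
- Counts 5, 5, 2 against 5, 0, 0: practices within a group disagree. The t-test gives t = (0.80 − 0.33)/0.389 = 1.2, p = 0.30. Permutation gives 8/20 = 0.40.

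**Step 4: floor of the exact practice-level test.** The smallest two-sided permutation p is 2/C(6,3) = 2/20 = 0.10 for 3 v 3, 1/C(6,2) = 1/15 = 0.067 for 2 v 4 and 1/6 = 0.167 for 1 v 5.

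**Step 5: could the ICC be this large?** For device insertion, suppose 3 of 6 practices offer LARC on site, 60% of their PCPs insert, and none do elsewhere. The mean is 0.3, the between-practice variance is 0.3² = 0.09 and the total variance is 0.3 × 0.7 = 0.21, so ICC = 0.09/0.21 = 0.43. At 40% inserting it is 0.04/0.16 = 0.25. These percentages are illustrative; recommendations may cluster less.

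**The case against.** The strongest reply is that little depends on these tests. The phase is mainly qualitative, and the tests are there to explore. There is no significance level, hypothesis or decision rule, and survey results are set beside interviews, observations and artifacts before anything is concluded. This stands, and it limits the severity.

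The harm also depends on an ICC that the article does not give, and at low values the test stays within nominal. Sampling PCPs for variety in their contraceptive practices could lower the ICC for that outcome if the variety were achieved within each site. No quota per site is stated, though, and recommendations would not be covered.

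The article does not define the practice attributes for relationship (2). An attribute reported by each provider could differ within a practice, and the point does not apply to it.

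A reader might infer more than the article supports:

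- **That the sample size for this question is really 6.** The effective number falls to 6 only at ICC 1. Having few practices limits inference, but that is a different statement.
- **That no practice attribute could reach 0.05 in a practice-level analysis.** This holds for exact permutation of practices only. The t-test in Step 3 reached 0.025, and with no true effect a t-test of this kind rejected in 4.4% to 6.0% of simulated studies (3 v 3, ICC 0 to 0.5).
- **That chance differences will be built into the tool.** No rule turns a p-value into a tool feature.
- **That relationships (1), (3) and (4) fail in the same way.** Their explanatory variables can vary within a practice. In simulation with an unclustered exposure, Fisher rejected 2.5% to 3.1% for outcome ICC 0 to 0.5. It passed 5% only when exposure and outcome both clustered strongly: 5.7% at 0.3 and 0.3, and 8.2% at exposure 0.3 with outcome 0.5. Testing within practice would cost power: for 0.3 against 0.8, from 72% to 65% with an unclustered exposure and from 71% to 45% at exposure ICC 0.3. That trade is debatable, and no change is asked for there.

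**Conclusion.** The point holds for relationship (2), for attributes that take one value per practice. The test and the relationship are both named in the article, so the mismatch is not a detail left to a fuller document. The planned p-values can overstate the evidence. At a nominal 0.05 the false-positive rate is clearly above nominal from an ICC of about 0.2 and reaches 20% to 25% at 0.5. These sizes rest on the assumed ICC, 5 PCPs per practice and a 0.05 level that the article does not set. Severity is moderate, because the tests are exploratory and secondary to the qualitative analysis. The conclusion does not extend to relationships (1), (3) and (4).

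**What to change.** In Data Analysis, separate relationship (2) from the other three. For any attribute constant within a practice, replace the provider-level Fisher test with a display of the proportion of PCPs in each of the 6 practices, grouped by attribute, and make no significance claim. If a p-value is wanted, use an exact permutation of practices and state its floor beside it (0.10 for 3 v 3, 0.067 for 2 v 4, 0.167 for 1 v 5). Mixed models and cluster-robust errors are not a good substitute, since they are unreliable with 6 clusters. List which attributes are fixed by practice, so that it is clear where the rule applies. Leave relationships (1), (3) and (4) as planned.

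The cost is that relationship (2) becomes descriptive. Recruitment, surveys and sample size do not change. Enrolment is under way, so the wording should be settled before the survey data are analysed.

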### Implications for Women With Chronic Medical Conditions

Women with chronic medical conditions (eg, diabetes and hypertension) have a higher rate of pregnancy-related complications [8-11] and death compared with women without these conditions [12,13]. The most prevalent chronic medical conditions (hereafter called “chronic conditions”) among reproductive-age women have risen over the last 10 years and include obesity (24.7%), asthma (16.2%), high cholesterol (13%), hypertension (10%), and diabetes (2.9%) [14]. Expanded definitions of chronic conditions that include psychiatric conditions estimate that women with chronic conditions comprise up to 45% of reproductive age women seen in primary care [15,16]. Studies have raised concerns that adult women with chronic conditions are at greater risk for unplanned pregnancy [17] as they are more likely to not use any contraceptive method, underutilize the most effective methods, and rely upon the least effective methods compared with the general population of reproductive-aged women [18-21]. Women with chronic conditions are often prescribed medications that can cause fetal defects [22,23], and those who do not desire pregnancy should be offered contraceptive options. Contraceptive counseling should include an explanation of potential beneficial or adverse impact of a method on their conditions and interactions with ongoing drug therapy.

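### Contraceptive use is compared across chronic conditions in all surveyed women, so any difference in pregnancy desire is mixed into the comparison

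*Protocol article*

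**What the plan says.** All references are to the protocol article.

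- **Data Analysis.** The method is fixed: "We will conduct bivariate analyses with Fisher exact test to explore the following relationships". Four relationships follow. The third is "the presence of different chronic conditions and current pregnancy desires among women" and the fourth is "the presence of different chronic conditions and current contraceptive use among women". No restriction, stratification or adjustment is given for the fourth. The abstract also names current contraceptive use as the patient outcome for Fisher testing.
- **Patients.** "Eligible patients must be women aged 18 to 50 years, fertile, English-speaking, and able to provide informed consent". A condition or drug criterion is added. Nothing is said about pregnancy intention. On the condition groups, "we aim to sample approximately equal numbers of women in the following groups"; three are named, and a further group takes less common conditions.
- **Sample Size.** "we aim to enroll 30 patients, 30 PCPs, and 30 staff members". The basis is qualitative: "6 to 12 interviews per homogeneous group provide sufficient qualitative data to reach saturation".
- **Implications for Women With Chronic Medical Conditions.** Of women with chronic conditions, "those who do not desire pregnancy should be offered contraceptive options".

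**The concern.** The fourth relationship puts every surveyed woman in one denominator. A woman who wants to conceive and uses no method counts as a non-user in the same way as a woman who wants to avoid pregnancy and uses no method. For a contraceptive decision tool these are different situations, and the article's introduction separates them.

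If pregnancy desire is similar across conditions, little is lost. If it differs, the condition with more women wanting pregnancy will tend to show lower use, even when women not wanting pregnancy use contraception equally in every group. The third relationship could reveal the imbalance but does not remove it from the fourth.

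What is at stake is interpretation. The survey results are to be merged with the interviews to identify factors that shape the tool. A crude percentage read as underuse in one condition group could point the design at a gap that is really a difference in pregnancy desire.

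**Working it through.** **The plan's own figure.** There is no power, alpha or effect size to reproduce. The only figure is 30 patients, justified by saturation. Four groups at 6 to 12 interviews give 4 × 6 = 24 to 4 × 12 = 48, which covers 30. Equal groups hold 30 / 4 = 7.5 women.

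**Formula.** Let d be the share of a condition group wanting pregnancy, u0 the use among women not wanting pregnancy and u1 the use among women wanting it. Then

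crude use = u0 × (1 − d) + u1 × d.

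With u0 and u1 the same in both groups, the crude gap is (u0 − u1) × (difference in d). The gap among women not wanting pregnancy is zero by construction.

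**Inputs.** The documents give no values for d, u0 or u1. All values below are assumptions, shown as a range.

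*Simple case, u0 = 70%, u1 = 0%:*

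| Desire | Crude use | Gap (points) |
|---|---|---|
| 25% v 10% | 0.75 × 0.70 = 52.5% v 0.90 × 0.70 = 63.0% | 10.5 |
| 30% v 5% | 0.70 × 0.70 = 49.0% v 0.95 × 0.70 = 66.5% | 17.5 |
| 40% v 10% | 0.60 × 0.70 = 42.0% v 0.90 × 0.70 = 63.0% | 21.0 |

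*Allowing some use among women wanting pregnancy:*

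| u0, u1 | Desire 20% v 20% | 10% v 30% | 10% v 50% |
|---|---|---|---|
| 80%, 5% | 0 | 72.5% v 57.5%: 15 points | 72.5% v 42.5%: 30 points |
| 80%, 20% | 0 | 74% v 62%: 12 points | 74% v 50%: 24 points |
| 70%, 10% | 0 | 64% v 52%: 12 points | 64% v 40%: 24 points |

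**Scale in women.** In a group of 7.5, 10.5 points is 0.105 × 7.5 = 0.8 of a woman, and 21 points is 1.6 women. In groups of eight under the simple case, two women wanting pregnancy v none already gives 0.25 × 70% = 17.5 points.

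**Effect on the test.** Exact enumeration of the two-sided Fisher test, with an assumed 0.05 level and 8 women with a condition v 22 without, gives these rejection rates over the three pairs of u0 and u1: about 3% with equal desire, 4% to 6% at 10% v 30%, and 15% to 26% at 10% v 50%. The effect would therefore show mainly in the reported percentages and less often as a small p value.

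**The case against.** The strongest reply is that the crude comparison is not wrong. If one condition group has more women wanting pregnancy and fewer users, its current use really is lower. Desire may lie between condition and use, and restricting to women not wanting pregnancy answers a different question. The phase 1 aim is to find factors for designing and implementing the tool. The fourth relationship is exploratory and is nowhere labelled unmet need. The tool will ask each woman about pregnancy and match its content to her answer. Every patient is also interviewed, and the qualitative strand is primary. Most of this stands. It limits the concern to interpretation and keeps it small, but it does not make the all-women figure the more useful one for a contraceptive tool.

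Two further defences are weaker. The sentence saying that a woman who desires pregnancy leaves the study belongs to the description of the path through the tool, which is built from phase 1 findings; it does not define the survey denominator. A fuller plan might refine the denominator, but the article itself states both a bivariate method and a population of women without restriction.

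A reader might also infer more than the documents support:

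- *That distorted differences will appear.* They arise only if desire differs by condition, and the article plans to explore that without asserting it.
- *That age drives both desire and use and must be stratified.* The documents offer no evidence for this. Splitting about 7 or 8 women per group by age as well as desire would make an exact stratified test nearly uninformative.
- *That the fertility criterion removes sterilized women, so the outcome is reversible-method use.* The article does not define the word, so no relabelling is warranted.

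**Conclusion.** The point holds in a limited form. The planned comparison combines women who want pregnancy with the women for whom the article says contraception should be offered, and nothing in the stated analysis separates them. If desire differs by condition, the crude percentages will reflect that difference as well as any difference in use among women avoiding pregnancy. Under the assumed rates above with unequal desire, the gap is 10.5 to 30 points with no difference among women not wanting pregnancy; with equal desire it is zero.

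The size rests entirely on assumed rates. The crude gap is a true description of current use and misleads only if read as underuse. It would be too strong to say that the analysis is biased or that the tool will be tailored to a false gap. This is a modest, low-cost improvement to an exploratory secondary analysis.

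**What to change.** Amend the fourth relationship in Data Analysis along these lines:

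> Current contraceptive use will be tabulated by chronic-condition group among women who report not currently wanting pregnancy. Women who are ambivalent and women who want pregnancy will be shown in separate rows. Use among all women will also be given as a crude description. Because cells are small, results will be reported mainly as counts and percentages.

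Pregnancy desire is already to be collected for the third relationship, so no extra recruitment is needed. The survey items are not shown; the separate row for ambivalent women assumes that the survey records ambivalence, as the planned tool does. No age-stratified exact test and no change to the outcome label are proposed.

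The cost is a few sentences and a smaller denominator for the main row. If 10% to 25% of 30 women want pregnancy (an assumption), 30 × 0.90 = 27 to 30 × 0.75 = 22.5 remain, less any ambivalent women. That is at most about 5.6 to 6.8 per group in four equal groups.
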